### Subgroup and exploratory analyses

Based on data from a pilot study, we anticipate that many of the children will have poor reading skills. This might impede their ability to comprehend the content of the textbook and to answer questions in the Claim Evaluation Tools. We will explore whether there are differences in the effect of the intervention for children with advanced reading skills (all four literacy questions in the evaluation tool answered correctly) versus basic reading skills (both basic questions correct and one or two of the advanced reading questions wrong) versus lacking basic reading skills (one or both of the basic reading skills questions wrong). We will conduct tests for interaction for the primary outcomes, and we will use published guidelines to interpret the results of these subgroup analyses [40, 41].

Parents of 500 children in each group will be recruited to participate in a parallel trial evaluating the effects of a podcast designed to teach the parents of primary school children in areas around the participating schools, concepts that they need to understand and apply to assess treatment claims [28]. We will evaluate whether the combination of the IHC primary school resources and podcasts improves outcomes compared to the primary school resources alone by testing for interaction between IHC primary school resources and the podcast in the statistical models as described above; the main effects of the podcast will also be included in these analyses.

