## Analysis

For the primary and secondary outcomes, we will use mixed models with a random effects term for the clusters and the stratification variables modelled as fixed effects, using logistic regression for dichotomous outcomes, linear regression for continuous outcomes and Poisson regression for count outcomes. For the questions that assess applied knowledge or understanding, missing values will be counted as wrong answers.

For each outcome, we will report the proportion, mean and standard deviation, or median and interquartile range for each group, the estimated difference, the estimated confidence interval for the difference, and the *p* value from the statistical model. For questions about intended behaviours and self-efficacy (see: Additional file 1), we will dichotomise the responses (e.g. ‘very unlikely or unlikely’ versus ‘very likely or likely’) in the analysis and we will report the proportions of children for each of the four response options.

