## Sample size

We used the University of Aberdeen Health Services Research Unit’s Cluster Sample Size Calculator [42] to calculate the sample size with the following assumptions:Children per cluster = 70Intraclass correlation coefficient (ICC) = 0.5, based on ICCs from a meta-analysis of randomised trials of school effectiveness which found ICCs to be higher than those reported for test scores in the USA [43]The proportion of children expected to achieve a passing score without the intervention, based on findings from pilot testing = 0%The smallest difference we want to be able to detect = 10%Alpha = 0.05Power = 90%

Based on these assumptions, we would need a total of 50 schools in each arm for the study to have 90% power to detect a difference of 10% between the two groups. Allowing for a loss to follow-up of up to 10% (for schools where it is not possible to administer the Claim Evaluation Tools at the end of the term), we estimate that we need a minimum of 55 schools in each group. This would provide more than 90% power to detect a mean improvement of one more correct answer for the 12 concepts covered by the primary school resources.

More specific information about the trial and the protocol is summarised in the Standard Protocol Items: Recommendations for Interventional Trials (SPIRIT) Checklist (see: Additional file 4).

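### The reading-skill interaction tests appear to rest on a model with one random term per school, which understates their standard error if the reading gap varies between schools (minor; exploratory analysis only)

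*Protocol article*

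**What the plan says.** The Analysis section gives one model family for all outcomes, primary and secondary alike: "we will use mixed models with a random effects term for the clusters and the stratification variables modelled as fixed effects". It is logistic for pass/fail and linear for the score. No other random term, robust variance or school-level analysis is mentioned anywhere in the protocol.

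The Subgroup and exploratory analyses section then introduces reading skill: "We will explore whether there are differences in the effect of the intervention for children with advanced reading skills". The comparison has three child-level categories, beginning with "children with advanced reading skills (all four literacy questions in the evaluation tool answered correctly) versus basic reading skills", so the interaction with arm has 2 degrees of freedom. It is to be tested on both primary outcomes: "We will conduct tests for interaction for the primary outcomes, and we will use published guidelines to interpret the results of these subgroup analyses".

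That sentence names no model. The next paragraph does so for the podcast interaction, which is to be examined by "testing for interaction between IHC primary school resources and the podcast in the statistical models as described above". For reading skill, use of the same model is therefore an inference, though the natural one: the outcomes are the same and no alternative is offered.

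**The concern.** Arm is a property of the school, while reading skill differs among children in the same school. The interaction therefore asks whether the within-school gap between reading groups differs, on average, between the arms. The independent units for that question are schools.

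A random intercept absorbs differences in school averages, but it cancels out of a within-school gap. With only that term, the standard error of the interaction reflects child-level noise and nothing else, so it is right only if every school in an arm has the same true gap. If some schools or teachers serve weak readers relatively better than others do, that variation is left out and the p value is too small. The confidence intervals for within-school subgroup contrasts are too narrow for the same reason.

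The protocol expects that many children will read poorly and that this may hinder both use of the textbook and answering of the questionnaire. A false reading-skill interaction could mislead readers about which children benefit.

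**Working it through.** **Inputs from the protocol (Sample size).** 70 children per school; ICC 0.5; 0% versus 10% passing; alpha 0.05; power 90%; 50 schools per arm, raised to at least 55 (110 in total).

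**Reproducing the plan's own figure.** Two proportions, 0 versus 0.10, two-sided, pooled variance: 98 children per arm. Design effect 1 + 69 × 0.5 = 35.5. Schools per arm: 98 × 35.5 / 70 = 49.7, so 50 as stated; 50 × 1.1 = 55. The protocol gives no figure for the interaction test, so there is none to reproduce.

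**Closed form for one contrast (1 df).** Let σ be the within-school SD of the score, τ the between-school SD of the true reading gap, m = 70, and q the share of children in one of two reading groups.

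- True variance of one school's estimated gap: τ² + σ²/[m q(1−q)].
- Variance counted by a model with a random intercept only: σ²/[m q(1−q)].
- Ratio: R = 1 + (τ/σ)² m q(1−q).
- Rejection rate with no true interaction: 2[1 − Φ(1.96/√R)].

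With q = 0.5, m q(1−q) = 17.5:

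- τ/σ = 0.1: R = 1.18, rejection 7%
- τ/σ = 0.2: R = 1.70, rejection 13%
- τ/σ = 0.3: R = 2.58, rejection 22%
- τ/σ = 0.5: R = 5.38, rejection 40%

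**Simulation of the 2-df test on the mean score.** 110 schools × 70 children, no true interaction, 1,500 runs per setting. Ranges run over ICC 0.2 and 0.5 and two assumed reading mixes (equal thirds; 50/30/20%). Stratum effects were left out; they are constant within a school and cancel from the gap.

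| τ/σ (assumed) | single school term | school-level gaps compared between arms |
|---|---|---|
| 0 | 4-5% | 4-6% |
| 0.1 | 6-8% | 5-6% |
| 0.2 | 11-13% | 4-7% |
| 0.3 | 21-23% | 4-6% |
| 0.5 | 42-43% | 4-6% |

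The Monte Carlo standard error near the upper ends at 0.1, 0.2 and 0.3 is √[p(1−p)/1500], about 0.7, 0.9 and 1.1 points. Rounding outward for this gives the working ranges 6-9%, 11-15% and 21-24%. On this scale the ICC hardly matters, because the intercept does not absorb variation in the gap.

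**Do the remedies hold 5%?** The last column is a test that lets the gap vary by school. In separate simulations a random school-by-reading-group term gave 4-6%, and school-level cluster-robust standard errors gave about 4-7%.

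**How large is such a τ?** If reading-group deviations are independent within a school, the correlation between a school's true means for two reading groups is V/(V + τ²/2), where V is the between-school variance.

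- ICC 0.5 (V = σ²): 1/1.02 = 0.98 at τ/σ = 0.2; 1/1.045 = 0.96 at 0.3.
- ICC 0.2 (V = 0.25σ²): 0.25/0.27 = 0.93 and 0.25/0.295 = 0.85.

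**Pass outcome.** Random-intercept logistic model, likelihood-ratio 2-df test, 500 runs per setting, assumed school SD of 1 on the logit scale, two assumed sets of pass rates. Rejection by logit gap SD: 0: 5-6%; 0.25: 7-9%; 0.5: 12-15%; 0.75: 25-32%; 1.0: 39-40%. The assumed control intercepts were −1.5 and −3, which is 18% and 5% passing in the reference reading group of an average school. Neither matches the planning value of 0% ("The proportion of children expected to achieve a passing score without the intervention, based on findings from pilot testing = 0"), so these rates show direction rather than size for this trial.

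**The case against.** Four points on the other side have force.

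- **The model is inferred.** Only the podcast interaction is explicitly tied to the stated models, and an analysis plan that is not shown could add a random slope. This stands as a caveat. It does not dispose of the point, because the protocol does state a random structure for these same outcomes, and that structure does not suit this use.
- **The size rests on an input the protocol does not give.** This stands. A reader might infer that the test rejects far above 5% as soon as the gap varies at all. The figures do not support that: at a gap SD of 0.1 within-school SD the rate is 6-9%, and it reaches about twice nominal only near 0.15 to 0.2. The high correlations between reading-group means also owe much to the ICC of 0.5; at 0.2 they are clearly lower.
- **The pass-outcome figures are weak.** This stands. If almost no control children pass, a logistic interaction is barely estimable whatever the random structure.
- **The stakes are limited.** The analysis is labelled exploratory, published guidelines are to govern its interpretation, and oral administration to a sample of children gives a separate check on literacy. This lowers the severity. Interpretation guidelines do not, however, repair a p value whose standard error is too small.

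A reader might also infer that the null hypothesis itself includes equal gaps in all schools. It does not. The null concerns the fixed interaction terms; equal gaps are an assumption of the standard error and reference distribution.

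**Conclusion.** The point holds as a minor one. Read naturally, the protocol tests a cross-level interaction with a model that leaves out between-school variation in the reading gap. The mean-score test holds about 5% if there is no such variation and is clearly inflated once the variation is moderate. This rests on 110 schools of 70 children, the assumed reading mixes and an assumed gap SD. For the pass outcome only the direction can be relied on.

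A reader might take this as a flaw in the main result. The documents do not support that: each primary comparison is between schools as randomised, and the random school term is there to account for clustering. The issue would also arise with a reading measure taken before the intervention, so it is separate from when reading skill is assessed.

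**What to change.** In the reading-skill interaction models for both primary outcomes, add a random school-by-reading-group term alongside the school intercept. Alternatively, keep the same fixed effects and use school-level cluster-robust standard errors, for which 110 schools are enough. The robust version is also the fallback if the logistic model does not converge, for example with very few passes in the control arm. Base the 2-df tests and the subgroup confidence intervals on whichever is used, and say explicitly which model serves the reading-skill tests.

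The cost is one sentence and one extra variance component, with no new data. The downside is somewhat wider intervals and less power for the interaction where the gap does vary, and possible convergence trouble in the logistic model.

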## Sample size

We used the University of Aberdeen Health Services Research Unit’s Cluster Sample Size Calculator [42] to calculate the sample size with the following assumptions:Children per cluster = 70Intraclass correlation coefficient (ICC) = 0.5, based on ICCs from a meta-analysis of randomised trials of school effectiveness which found ICCs to be higher than those reported for test scores in the USA [43]The proportion of children expected to achieve a passing score without the intervention, based on findings from pilot testing = 0%The smallest difference we want to be able to detect = 10%Alpha = 0.05Power = 90%

Based on these assumptions, we would need a total of 50 schools in each arm for the study to have 90% power to detect a difference of 10% between the two groups. Allowing for a loss to follow-up of up to 10% (for schools where it is not possible to administer the Claim Evaluation Tools at the end of the term), we estimate that we need a minimum of 55 schools in each group. This would provide more than 90% power to detect a mean improvement of one more correct answer for the 12 concepts covered by the primary school resources.

More specific information about the trial and the protocol is summarised in the Standard Protocol Items: Recommendations for Interventional Trials (SPIRIT) Checklist (see: Additional file 4).

## Safety monitoring and adverse events

The National Council of Science and Technology in Uganda has given this study a very low rating for risk to participants. Nonetheless, we will monitor unexpected adverse events and problems that might pose risks to the children or others by asking teachers to record these and report them to the investigators or, if relevant, to the Makerere University College of Health Sciences Institution Review Board. Teachers in the intervention arm of the trial will be given contact information at the start of the trial and instructions for recording adverse events and problems in the journals that they will be asked to keep (see: Additional file 5).

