### Random allocation

Schools will form the basic units (clusters) for allocation. Each school will be numbered and listed, and the study arm allocation will be determined using computer-generated randomisation, with equal numbers of the schools allocated to each arm in each stratum.

A statistician who is not a member of the research team will use computer-generated allocation sequences (www.sealedenvelope.com) to randomly allocate schools to either the control or intervention arm. No changes to allocation will be made subsequent to this.

We will use a block size of 4, with equal allocation ratios in each block and strata. The lists for each district will be randomly generated as shown in the table below (Table 1).

**Table 1 Tab1:** Examples of random allocation sequence

Block identifier	Block size	Sequence within block	Treatment	Location	Ownership	Code
1	4	1	Group A	Rural	Government	FZ4
1	4	2	Group A	Rural	Government	MG9
1	4	3	Group B	Rural	Government	NC5
1	4	4	Group B	Rural	Government	ID9
2	4	1	Group B	Rural	Government	VO9
2	4	2	Group B	Rural	Government	UA4
2	4	3	Group A	Rural	Government	KB5
2	4	4	Group A	Rural	Government	OQ6

As shown above (Table 1), the statistician will prepare a randomisation list with unique codes and corresponding allocation groups for each participating school. We will prepare separate lists for each stratum; i.e. rural-government for a rural school owned by government, rural-private for a rural school owned privately; suburban-private for a suburban school that is owned privately, suburban-government for a suburban school that is owned by government, urban-private for an urban school owned privately, and urban-government for an urban school that is government owned. These will contain only the participant school’s study code. Study allocation groups (intervention or control) corresponding to each study code will be inserted in envelopes and sealed. Every envelope will contain its study code as a label. For example, if the school is located in a rural area and it is a government school, a list will be prepared from the general list for that particular district. Below is an example of the study groups with corresponding study codes (Table 2).

**Table 2 Tab2:** Example of study groups and corresponding study codes

Treatment	Code
Group A	FZ4
Group A	MG9
Group B	NC5

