### Delivery of the intervention

We will contact participating schools 2 to 3 months before the start of the trial and invite all participating teachers in the intervention group to attend a 2-day introductory meeting. At the meeting we will inform them about the study objectives and procedures, including the Claim Evaluation Tools that we will use as an outcome measure, introduce them to the IHC primary school resources, and address any queries or concerns that may arise. We will discuss the general nature of the evaluation tool, but will not give the teachers copies of the questionnaire. We will try to contact or visit all the teachers in the intervention group who are unable to attend a meeting.

At least 1 week before the trial commences (and prior to the introductory meeting) we will give teachers in the intervention group the teachers’ guide to enable them to familiarise themselves with the content and prepare a semester plan for delivering the lessons. We will deliver the textbooks to the schools in the intervention group at least 1 week before the trial starts. We will use class lists provided by the school heads to ensure that each school receives an adequate number of books for all the primary-five children in the school.

To help ensure that the intervention is delivered as planned, we will monitor delivery of the intervention. We will do this by following guidelines of the Ministry of Education school supervisory timetable. These allow for follow-up of newly introduced programmes within schools [34]. We will encourage the teachers to make summaries after reading each chapter in the teachers’ guide in preparation for the lesson and we will ask them to hand these in to the study team after the intervention period. This will help to ensure that the teachers read the teachers’ guide in preparation for the lessons.

We will contact the schools allocated to the control group at the beginning of the school term to inform them about the study and study procedures and the evaluation tool that we will use as an outcome measure. We will tell them that they will receive the IHC primary school resources at the end of the study, but we will not introduce them to the resources or invite them to the introductory meeting.

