## Blinding

The comparison will not be blinded. All of the participants in the trial will be informed of the purpose of the study and will know whether they are in the intervention or control arm. The head teachers and the district education officers will be informed of the purpose of the study when they are recruited. The primary-five teachers in both arms of the trial will be informed of the purpose of the study prior to the delivery of the intervention. Children in both arms of the trial will be informed of the purpose of the Claim Evaluation Tools when they are asked to complete them. They will also be asked to put their names on the questionnaires and will be told that they and their teachers will be told their scores.

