## Discussion

So far as we are aware, this is the first randomised trial to evaluate the effects of an intervention to teach key concepts that are essential to improving people’s ability to critically assess claims made about the effects of treatments to primary school children [18–21]. It is unlikely that the IHC primary school resources alone will have a measurable effect on health outcomes. Primary school children do not make many decisions on their own, and there are many other factors that affect decision-making and health behaviours. Nonetheless, these skills are essential for informed participation in personal and societal health care decisions, as well as for coping with the flood of information making claims about treatment effects.

It is important to introduce these key concepts at a young age to lay a foundation for future learning. Whether what is learned is sustained or not, it would be desirable to reinforce what is learned and to introduce additional key concepts as part of a spiral curriculum [44]. Thus, it is important to evaluate whether the resources have an important effect on children’s ability to assess treatment claims, regardless of whether this has a measurable impact on health or how long what is learned is retained. If there is an important effect, the implication will be that consideration should be given to using these resources, or similar interventions, and to build upon this in the future. If there is not an important effect, consideration should be given to why they did not work and how to design a more effective intervention. We will conduct a process evaluation to explore why the resources did, or did not, have intended effects and explain variations in effects [45]. In the process evaluation, we will also explore other potential adverse and beneficial effects than those that were measured in this trial, ways in which use of the primary school resources could be scaled up (assuming they are effective), and the impact of the intervention on teachers and parents.

In summary, we believe that the findings of this trial will have important implications for children, their parents and teachers, head teachers, policy-makers, and anyone with an interest in health literacy or evidence-informed decision-making.

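### Adverse-event recording tools are described for intervention-arm teachers only, so event counts would probably not be comparable between arms

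*Protocol article*

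**What the plan says.** The protocol article, under Safety monitoring and adverse events, commits the trial to monitoring unexpected events and problems "by asking teachers to record these and report them to the investigators" or, where relevant, to the review board. That sentence names no arm. The next sentence supplies the means and names one arm: "Teachers in the intervention arm of the trial will be given contact information at the start of the trial and instructions for recording adverse events". The entries go into a journal kept by these same intervention-arm teachers.

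Under Delivery of the intervention, control schools are contacted at the start of term to "inform them about the study and study procedures and the evaluation tool that we will use as an outcome measure". Adverse-event recording is not mentioned there, and of these schools the article says "we will not introduce them to the resources or invite them to the introductory meeting".

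Under Blinding: "The comparison will not be blinded". Under Random allocation, the design has "equal numbers of the schools allocated to each arm in each stratum". The Discussion adds that in the process evaluation "we will also explore other potential adverse and beneficial effects than those that were measured in this trial", without describing a comparison between arms.

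**The concern.** The people who report events know their arm, and only one group of them is described as receiving a contact route, instructions and a journal. A count gathered by prompting in one arm and without described prompting in the other reflects how events were looked for as well as how often they occurred. The monitored category is broad, since it covers problems as well as adverse events, so it will pick up ordinary school-term occurrences. Only a control count collected in the same way could show how much of the total is background.

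Two things are at stake. First, if events are reported at the end of the trial, they could neither be attributed to the lessons nor used to say that the lessons caused no excess. Second, control children also take part in study procedures: under Blinding, children in both arms put their names on the questionnaire and are told that their teachers will learn their scores. If a problem arises in a control school, the article describes no working instrument for reporting it.

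**Working it through.** The article states no adverse-event rate or count, so there is no figure to reproduce. The check sets the relevant sections side by side and then asks what an observed count could mean.

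**What each arm's teachers are described as receiving**

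| Item | Intervention arm | Control arm | Section of the protocol article |
|---|---|---|---|
| General request to record and report | Yes (no arm named) | Possibly (no arm named) | Safety monitoring and adverse events |
| Contact information at the start | Yes | Not described | Safety monitoring and adverse events |
| Recording instructions | Yes | Not described | Safety monitoring and adverse events |
| Journal for entries | Yes | Not described | Safety monitoring and adverse events |
| Introductory meeting | Invited | Not invited | Delivery of the intervention |
| Knowledge of allocation | Yes | Yes | Blinding |
| Attendance and examination marks compared | Yes | Yes | Outcome assessment; Secondary outcomes |

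**What an observed ratio would mean.** Let r1 and r0 be the true event rates in the intervention and control arms, and s1 and s0 the fractions of events that reach the investigators. Equal numbers of schools are allocated to each arm, so treat the two denominators as about equal (an assumption, since school sizes vary). Then:

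- expected observed ratio = (r1 × s1) / (r0 × s0) = (r1/r0) × (s1/s0).
- With equal true rates (r1 = r0), this reduces to s1/s0.
- With equal capture (s1 = s0), it reduces to r1/r0, the quantity of interest.

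The article gives none of the four values. One observed ratio cannot be split into its two factors, and the table gives no ground for setting s1 = s0. If the true rates are equal and capture in the intervention arm is at least as good as in the control arm, the apparent ratio runs from 1 (equal capture) upwards without limit as s0 approaches zero. The article does not narrow that range. The direction of the distortion is therefore likely to be upwards for the intervention arm, but its size is unknown.

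**Whether another part of the plan fills the gap.** Attendance and end-of-term marks are compared in both arms, which covers foreseeable unwanted effects such as displaced teaching time. They do not record unexpected events. The process evaluation in the Discussion is exploratory, and no control-arm event count is described for it. Additional file 5 is not shown; it is cited for the intervention-arm journals, and nothing in the text extends it to control schools.

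**The case against.** The strongest reply is that this monitoring exists so that somebody can act on a problem, not to estimate a rate ratio. Adverse events are not among the objectives or the primary or secondary outcomes, and no section promises a between-arm event figure or a no-harm statement. This stands, and it is the main reason the point is small. It does not remove the point: once events are collected and reported, readers will want to know whether they exceed background, and the described procedure could not tell them.

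The sentence asking teachers to report names no arm, so some control reporting is possible. This also stands. A reader might infer that control children have no reporting route at all, and the text does not support that. What is missing is any described operational means for control teachers. That the tools go to one arm only is inferred from the control arm not being mentioned.

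A reader might also infer that the intervention arm is bound to show more reports whatever the true rates. That does not follow. With few or no events, or with a sufficiently higher true rate in control schools, it need not happen. Nor should a number be put on it: assumed capture fractions of 80% and 10% would give 80/10 = 8 to 1 under equal true rates, but nothing in the article supports either fraction.

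Finally, the control-arm hazard is slight. Control schools keep their usual curriculum, and their children's main study exposure is a one-hour test run like an ordinary school examination, which intervention children also take. This is fair, and it limits the practical weight further.

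**Conclusion.** The point holds in a limited form. As written, the article describes unequal means of recording adverse events in an open trial, so capture is likely to differ between arms and the counts should not be compared. Reports from the lessons could not be separated from ordinary school-term background, and control teachers lack a described working means of reporting.

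No size can be given. The conclusion rests on two assumptions: that the silence about control teachers means no equivalent materials are planned for them, and that prompting with instructions and a journal raises capture. The very low risk rating, the absence of a planned event comparison, and the two-arm comparison of attendance and academic achievement keep the consequence modest. The primary outcomes, the sample size and the main analysis are not affected. This is a worthwhile improvement, not a flaw that threatens the trial's main result.

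**What to change.** Give primary-five teachers in both arms the same contact information and the same short event form, covering the same reporting period. Hand it out with the baseline teacher form, which teachers in both arms already complete (Data collection and management), and collect it when research assistants pick up the end-of-term questionnaires. Report event counts by arm from that form alone, and report lesson-specific problems from the intervention journals separately, without comparing them.

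If this is not done, add one sentence stating that events are described for the intervention arm only and that no comparative or no-harm conclusion will be drawn from them.

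The cost is one printed page per participating teacher, at contacts already planned. With the 120 schools in the abstract split equally, that means 120/2 = 60 control schools. The downside is a small extra task for control teachers. Identical forms will not make reporting fully equal, because teachers know their arm and intervention teachers also keep a journal, but the two counts would at least come from the same instrument.
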